## *Informed Consent Process*

Potential participants will be informed (in the language of their choice – English, Spanish, Swahili, Kirundi, Kinyarwanda, or French) about the study purpose, procedures, risks, and benefits. They will be informed that their participation is voluntary, that they can decline to participate, that they are free not to answer any question, and that they can withdraw at any point without negative consequences. The alternative to participation is not to participate. Potential participants from community-based organization (CBO) partners will be assured that their decision to participate or not to participate will not affect their receipt of any services from the CBO. At the time participants consent, they will be asked to provide their name, address, phone number, email address, and the phone numbers and email addresses of at least two people who would know how to locate them in 8 months. Study participants will also be informed about the participant compensation ($25-$70 for each successive survey and $25 for each qualitative interview).

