## *Data Collection Procedures*

Quantitative survey procedure. All 1300 participants will complete 5 surveys over 32 months. LD Insights and the UNM study team will use Computer-Assisted-Telephone-Interviewing (CATI) and Computer-Assisted Self-Interviewing (CASI) protocols. CATI and CASI programming will be completed by LD Insights staff. LD Insights phone and web-based survey procedures are detailed previously. UNM bilingual study team members will follow a similar protocol (CATI over the phone or web-based CASI emailed to participant), depending on participant preference and literacy. Compensation for participants’ time for each survey will start at $25 and increase as follows: T1 $25, T2 $40, T3 $50, T4 $60, and T5 $70. Increasing payments over time improves retention in longitudinal studies.^82,83^ The survey will include well-validated measures from PhenX Toolkit, except when noted due to lack of appropriate measure (see Table 1). Our research team has extensive experience ensuring culturally appropriate measurement of mental health; we expect the measures we have chosen to be relevant and efficient and to maximize our opportunity to understand intervention effects on multiple dimensions of psychological distress. Single-item questions from PhenX to measure demographic, control, and moderator variables are: biological sex assigned at birth, gender identity, sexual orientation, age, race/ethnicity, birthplace, years living in U.S., annual family income, marital status, employment status, educational attainment, health insurance coverage, household roster/relationships, and English proficiency. Survey questions will also obtain additional information needed for propensity score matching by asking about factors likely to predict involvement with CBO partners: length of residence in NM, having children in schools, use of community services, and religious service attendance. Most measures have been used with Spanish-speaking immigrants; we will translate measures into Kiswahili using a team approach, following the TRAPD (Translation, Review, Adjudication, Pretesting, and Documentation) process.^70,71^ The survey will be piloted in all languages to ensure comprehension, appropriateness, and length of 30-40 minutes or less.

| Table 1. Quantitative Measures | | | |
| --- | --- | --- | --- |
| **Variable** | **Measure** | **Detail** | # of Items & Psychometrics |

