**Aim 2**. Test the effects of engagement with CBOs to reduce adverse consequences of the COVID-19 pandemic. Analyses will use both the CBO sample and the random sample of Latinx respondents from across the state. The primary predictor is whether the participant is recruited through the CBO or random community sample. Our analyses test whether respondents recruited from CBOs differ from those in the random sample in outcomes and whether those differences change over time. While the comparison sample is a random probability sample of Latinx immigrants, the CBO sample consists of respondents already connected to a CBO, thus we propose to use propensity score matching^101,102^ with data collected at baseline to match those in each sample. The matched samples used for data analysis will adjust for systematic differences between the random sample and those who engage with CBOs. Our baseline measures have been chosen to include variables which are likely to predict an individual’s exposure to a CBO. To examine the effects of engagement with CBOs, we propose a longitudinal model with random effects for both individuals and CBOs. The model will also adjust for effects of the RIWP intervention observed in Aim 1. We note that the adjustment for clustering within CBOs only takes place for those in the CBO arm; in the comparison arm where there is no nesting, these random effects are assumed to be zero.^103,104^ In mixed notation the model for psychological distress is:

${Distress}_{tij}= B_{000}+{\gamma_{001}\left( CBO \right)+{B_{100}\left( Time \right)+\gamma_{101}\left( CBO*Time \right)\boldsymbol{+B}}_{\boldsymbol{010}}\left( \boldsymbol{covariates} \right)+{B_{020}\left( RIWP \right)+B_{030}\left( RIWP*Time \right)+ u_{00j}+u}_{10j}\left( Time \right)+r_{0ij}+r_{1ij}(Time)+ e}_{tij}$

where CBO is an indicator indicating whether individual *i* is engaged with the CBO, Time is a variable indicating the time of observation in years. For this analysis, Time will be centered around the midpoint of the study because engagement with the CBO is ongoing from before the study began. Thus, our aim is answered by Y_001_ which is the difference in mean levels of distress, adjusted for covariates, between those who experience the CBO and those in the random sample and by Y_101_ which is the difference in slopes over time between those who experience the CBO and those in the random sample.

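### No listed survey item records where in New Mexico a participant lives, so the Aim 2 and Aim 3 estimates of the CBO effect can be confounded with place

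*Protocol*

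**What the plan says.** Under Data Collection Procedures, the protocol names 14 single-item demographic, control and moderator variables, among them "annual family income, marital status, employment status, educational attainment, health insurance coverage, household roster/relationships, and English proficiency". It then says the survey will obtain "additional information needed for propensity score matching by asking about factors likely to predict involvement with CBO partners", and names four: "length of residence in NM, having children in schools, use of community services, and religious service attendance". Length of residence is a duration, not a location. Table 1 adds eight outcome and covariate domains, none of which is geographic.

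The Aim 2 text in Data Analysis/Statistical Considerations says "Analyses will use both the CBO sample and the random sample of Latinx respondents from across the state", and notes that "the CBO sample consists of respondents already connected to a CBO". It relies on matching to deal with this: "The matched samples used for data analysis will adjust for systematic differences between the random sample and those who engage with CBOs". The Aim 2 model has no geographic term, and its CBO random effects are set to zero in the comparison arm. Aim 3 is described as similar to Aim 2 with a logit link; its outcome is access to relief policies that may be local or state-level.

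Place does enter the study in one way. At consent, "they will be asked to provide their name, address, phone number, email address". But Data Management Procedures and Confidentiality says these details serve tracking only and are stored apart from the interview and intervention data. The list linking names to study numbers is to be destroyed before the study closes.

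**The concern.** A propensity score balances the samples only on what goes into it. One sample is recruited through the classes, groups, services and meetings of five organizations; the other is drawn statewide. Where someone lives could influence both whether they become a client and how they fare on distress, stressors and economic precarity. It can also decide whether a local relief measure is open to them at all. Without a place variable, two people can be well matched on every listed item and still live under different local conditions.

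The exclusion rule could widen any gap. The random sample leaves out anyone who used one of the four Latinx-serving organizations in the past year. If users cluster near the sites, this removes some comparison members from those areas.

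The protocol itself allows that outcomes vary by area: the ICC of .03 in its Power section is taken from literature on clustering within neighborhoods. At stake is whether a difference reported as the effect of CBO engagement is partly a difference between areas. A larger random sample does not help, since it shrinks the standard error but not the bias.

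**Working it through.** **1. The plan's own figure.** Inputs from the Power section: d = .30, baseline–posttest correlation .68, ICC .03, attrition 10% (CBO) and 30% (random sample). Two-sided alpha of .05 is assumed, as none is stated.

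- Residual variance = 1 − .68² = .5376; residual SD = .733.
- With 270 CBO participants (300 less 10%), 210 in the random sample (300 less 30%), five CBOs and the ICC applied to residual variance: SE² = .03 × .5376/5 + .5376/270 + .5376/210 = .00323 + .00199 + .00256 = .00778, so SE = .0882.
- Power = Φ(.30/.0882 − 1.96) = .925, against .92 stated.
- With 700 in the random sample (1000 less 30%), SE = .0774 and power = .972.

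The stated figure is reproduced. It contains no allowance for confounding.

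**2. Which terms place can reach.** Let g be the difference between samples in the share living in the CBO areas. Let the area effect remaining after matching be a + c × Time, with Time centered at mid-study as in the Aim 2 model. Then:

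- bias in the level contrast = g × a;
- bias in the slope contrast = g × c, which is zero if the area difference is stable.

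The CBO random effects are zero in the comparison arm, so they cannot absorb a difference between the samples. Aim 1 compares arms randomized within CBO site, so place does not confound it.

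**3. Illustrative size, Aim 2 level.** Neither g nor a is in the documents; both are assumed. Take g = .10 to .65 and a = .1 to .3 SD.

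- Lowest: .10 × .1 = .01 SD.
- Middle: .50 × .2 = .10 SD, one third of .30.
- Highest: .65 × .3 = .195 SD.

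Using the standard errors from step 1 as a rough scale, the chance of a significant CBO effect when none exists is:

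| Bias (SD) | 210 in random sample | 700 in random sample |
|---|---|---|
| .01 | .051 | .052 |
| .06 | .104 | .121 |
| .10 | .205 | .253 |
| .15 | .398 | .492 |

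**4. Illustrative size, Aim 3.** The protocol gives a comparison-group rate of .2 and a target odds ratio of 2. Assume 40% of the random sample and 50–90% of CBO clients live in the CBO areas, with an area odds ratio of 1.5–3 and no true CBO effect. Worked case at 90% and 3:

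- The rate outside the areas is .129 and inside .307, since .4 × .307 + .6 × .129 = .20.
- The CBO-group rate is .9 × .307 + .1 × .129 = .289, with odds .407.
- The spurious odds ratio is .407/.25 = 1.63.

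The mildest case (50%, area odds ratio 1.5) gives 1.04.

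**5. Numbers left if matching is exact on area.** If 35–70% of the random sample lives in the CBO areas (assumed), 350–700 of 1000 remain. After 30% attrition that is 245–490. The 240 Latinx CBO participants less 10% are 216.

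**The case against.** The strongest reply is that the matching set is not closed. The four items are described as additional, the Aim 2 text speaks generally of baseline data, and the choice of propensity covariates is commonly left to a statistical analysis plan. Address is collected, so an area code could be made. This stands in part: the protocol does not forbid the use of place. But an analysis plan can use only what reaches the analysis file. As written, place does not, and the link to the address is eventually destroyed.

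A reader might also infer several stronger things that the documents do not support.

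- **That the CBOs serve particular localities, so the effect is mixed with place.** No location or catchment is given. Two of the four Latinx-serving organizations, supplying 120 of the 240 Latinx CBO participants, have statewide names. Names do not prove reach, but CBO activities were also remote when the protocol was written. The samples may have a similar area mix, in which case the bias is zero.
- **That nearness is the strongest predictor of being a client.** This is plausible, but nothing in the text ranks predictors.
- **That the Aim 2 slope is biased as well as the level.** A stable area gap cancels from the slope.
- **That the Aim 2 matched sample is reused in Aim 3.** The text says only that the analyses are similar.

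Finally, income, employment, education, insurance and use of community services may stand in for part of any area difference. That is why the area effect in the illustration has to be read as what remains after matching. These items are less likely to capture whether a local relief measure exists where a person lives.

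**Conclusion.** The gap is real, and its effect is conditional. The listed survey content has no measure of residence, and address is kept out of the interview data, while the Aim 2 text expects matching to remove systematic differences from a "random sample of Latinx respondents from across the state". The CBO effect can therefore be confounded with place; the documents do not show that it is.

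Most exposed are the Aim 2 level contrast and, in Aim 3, access to local relief. The range of about .01–.20 SD, and the spurious odds ratio of 1.04–1.63, rest entirely on assumed area mixes and area effects, and both vanish if the mixes agree or area has no effect. The rejection rates borrow standard errors from the simplified pre/post calculation, not the full longitudinal model, so they indicate scale only. The principal objective, Aim 1, is untouched. The change is worth making because it is cheap now and cannot be made once the linking list is gone.

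**What to change.** Add one coarse area item to the T1 survey (county, region, or urban/rural). Alternatively, derive such a code from the address before the linking list is destroyed and attach only that code to the analysis file. Include it in the propensity model for Aims 2 and 3 and report balance on it. Exact matching on area is an option, or a sensitivity analysis, if overlap allows; it need not be the primary approach.

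The cost is one item or one derived variable, with two drawbacks. First, an area code enters the data file. It must be reconciled with the commitment under Potential Risks to keep identifiable data to a minimum, and with the separation of address from interview data under Data Management Procedures and Confidentiality. A coarse code is less identifying than the address already held. Second, some random-sample members outside the CBO areas may go unmatched. With exact matching and the low end of the assumed range, 245 against 216 is close to one-to-one before any other variable is matched, which favors using area as a propensity covariate first.

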## *Participant Enrollment*

Total enrollment is 1300: 1240 Latinx immigrant adults and 60 African refugee adults. The participants will be Latinx immigrant and African refugee adults (ages 18 and above) who are living in New Mexico. They will participate in the longitudinal study with 5 timepoints of survey data collection over 32 months (at 8 month intervals). Of this total number, 1000 Latinx immigrants will be a random sample comparison group recruited by LD Insights/Latino Decision. The other 240 Latinx immigrants and the 60 African refugees will be recruited through 5 CBO partners, and, in addition to the 5 same timepoints of survey data collection, will be randomly assigned after the first timepoint of data collection to the 16-week RIWP intervention or to a treatment-as-usual (TAU) waitlist control group (who will receive the RIWP intervention in Year 3). A purposive subsample of 36 participants [15 from RIWP intervention group (12 Latinx and 3 African), 15 from TAU group (12 Latinx and 3 African) and 6 from RS (random sample comparison group)] will participate in qualitative interviews at all 5 timepoints. Approximately equal numbers of men and women are anticipated. All 240 Latinx immigrant adults and 60 African refugee adults enrolled in the study through CBOs will be eligible for participation in the intervention study. Exclusion criteria will be severe cognitive functioning problems or mental illness that is so severe as to impede participation in a group and that warrants immediate individual treatment. Excluded adults (except those with cognitive functioning issues already being addressed or those already in treatment) will be referred immediately for individual treatment.

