Random assignment. Randomization of the CBO-recruited sample (n=300) into RIWP or treatment-as-usual waitlist control group (TAU) will occur after completion of timepoint 1 surveys and will be based upon a computerized algorithm that stratifies randomization by CBO site.

RIWP implementation. RIWP will be implemented with 30 participants from each CBO site (n=150) from Months 5-12. RIWP will be integrated into existing activities and services in different ways at each site, with the goal of creating a sustainable intervention and multilevel change. All RWIP activities (Learning Circles and advocacy) will be conducted remotely for now. Once state and UNM COVID restrictions are lifted, some in-person Learning Circles and advocacy meetings may occur. The treatment-as-usual waitlist control group will participate in RIWP after two years (3 timepoints) of data collection, from Months 29-35. RIWP involves a sustainable and replicable partnership model between refugees, CBOs, and universities (see Figure 1 for conceptual model). Newcomer families and undergraduate advocates work together for 16 weeks to: a) increase newcomers’ abilities to navigate their new communities; b) improve newcomers' access to community resources; c) enhance meaningful social roles by valuing newcomers' cultures, experiences, and knowledge; d) reduce newcomers' social isolation; and e) increase community responsiveness to newcomers. RIWP is implemented by university students enrolled in a 2-semester course, and has two elements: 1) Learning Circles, which involve cultural exchange and one-on-one learning opportunities; and 2) Advocacy, which involve collaborative efforts to mobilize community resources related to health, housing, employment, education, and legal issues and to create policy/system changes. Meeting in weekly Learning Circles, newcomers and their student partners learn from each other during cultural exchange time designed to facilitate sharing of cultural and intergenerational knowledge and to help newcomers recognize their contributions and potential to effect changes in their communities. During one-on-one learning time, newcomer and student participants practice English, fill out job applications, and engage in other activities newcomers want to pursue to expand knowledge, improve skills, or accomplish goals. RIWP is holistic, multilevel, and strengths-based, and has an explicit social justice orientation that is informed by an ecological perspective. A holistic intervention is essential because it addresses the multiple sources of newcomers’ psychological distress, including psychological (past traumas), material (poverty, lack of access to resources), physical (physical ailments from war, violence and deprivation), social (loss of meaningful social roles and social support), educational (limited English proficiency, literacy), and cultural disconnection from traditional cultural practices). A strengths-based perspective is important because newcomers have survived in the face of tremendous hardships and have numerous strengths on which to build, including cultural knowledge (and often extensive cross-cultural experience), resourcefulness (experience operating in resource scarce situations), effective coping strategies (that have enabled them to survive), multilingual abilities (many arrive already speaking two or more languages), and often strong family and community bonds and support. Newcomers are often pathologized by well-intentioned service providers and systems, rather than recognizing that most are resilient people who have faced abnormally difficult circumstances. Not only is it crucial for newcomers’ mental health and well-being to acknowledge their expertise and build upon their strengths, but also their knowledge and experiences are assets from which other Americans can benefit. Thus, mutual learning is an intentional and core component of RIWP. This emphasis also ensures that RIWP is appropriate for multiple linguistic and cultural groups who can participate simultaneously and learn from one another as well as from longer-term residents of the U.S. Guided by ecological theory, RIWP focuses not only on newcomers adjusting to their new contexts, but also on changing environments when they are inequitable or constraining (e.g., mobilization or redistribution of resources). Ensuring that RIWP creates change at multiple levels is important because newcomers have urgent learning, resource, and health needs that must be addressed at the individual level in order to enable them to work collectively with others to create community and structural changes that address the root causes of mental health disparities and social inequities, which result in sustainable social change.

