This study is specifically designed to be sensitive to the changing impacts of the pandemic and the effectiveness of the multilevel interventions in reducing those. Thus, we propose 5 data collection points, every 8 months over 32 months. Our primary outcomes – psychological distress, daily stressors, and economic precarity – tend to be moderately stable^93–98^ but may also be impacted by shocks such as losing a job or getting COVID-19. Given the unknown trajectory of the pandemic and the path of economic recovery, we do not know a priori what the best approach to use for the longitudinal data will be. Therefore, our proposal is to use those in the random comparison sample in order to explore longitudinal models which will capture a large portion of the variability in outcomes over time while also maximizing power to find treatment effects. For example, modeling effects on mean levels of the outcomes post baseline would involve only 1 model parameter but would miss much of the nuance in the data. The comparison respondents will allow us to examine possible alternatives (linear change, piecewise change, adjustments for time-varying events including unemployment and COVID infections) in data without treatment effects. We will conduct analyses and publish a paper which examines fit of alternative longitudinal models to the data, and we will conduct additional power analyses before choosing the approach which best balances model fit and power. For the remainder of the data analysis section, we assume a relatively simple model with an intercept and linear change, while power analyses assume a simple pre-post design which will result in conservative estimates of power.

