**Aim 1.** Test the effects of the RIWP intervention to reduce adverse consequences of the COVID-19 pandemic. The principal objective of this study is to test the efficacy of the RIWP intervention for participants recruited from CBOs. Because only individuals recruited from the CBO sample are eligible to be randomized to receive the RIWP intervention or treatment as usual, analysis for this aim includes only CBO participants. To examine the effects of the RIWP intervention, we propose a linear model with random effects for individuals. As randomization happens within CBO, there is not an explicit random effect for this included, but we do propose to use sandwich estimators,^99,100^ to adjust standard errors for any unexpected impacts of this clustering. In mixed notation the model for psychological distress is:

${Distress}_{ti}= B_{00}+{B_{01}\left( RIWP \right){+B}_{02}\left( Time \right){+B}_{03}\left( Time*RIWP \right){+\boldsymbol{B}}_{\mathbf{0}\boldsymbol{N}}\left( \boldsymbol{covariates} \right)+ r_{0ij}+r_{2ij}(Time)+ e}_{ij}$

where participation in the RIWP plus CBO is indicated by a dummy code for RIWP. Because baseline data is collected before randomization, time is centered at baseline and our aim is answered by B_03_ which is the difference in slopes of levels of distress, adjusted for covariates, between those who experience RWIP+CBO intervention and those in the CBO group.

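### The waitlist arm receives RIWP before or during T5, but the only Aim 1 test written down (the slope difference B03) neither excludes T5 nor codes that exposure, so an early, sustained benefit is attenuated.

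*Protocol*

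**What the plan says.** **Schedule.** The Data Analysis section gives the survey plan: "we propose 5 data collection points, every 8 months over 32 months". Under Data Collection Procedures, randomization of the CBO sample "will occur after completion of timepoint 1 surveys". For the intervention arm, "RIWP will be implemented with 30 participants from each CBO site (n=150) from Months 5-12". For the control arm, "The treatment-as-usual waitlist control group will participate in RIWP after two years (3 timepoints) of data collection, from Months 29-35". Participant Enrollment describes the control arm as those "who will receive the RIWP intervention in Year 3".

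**Analysis.** For Aim 1, "time is centered at baseline and our aim is answered by B_03_ which is the difference in slopes of levels of distress". The model has a fixed dummy for RIWP, linear time, their product and covariates. It limits the analysis to CBO participants but says nothing about which waves enter. The Aim 2 equation contains RIWP and RIWP by time, introduced by "The model will also adjust for effects of the RIWP intervention observed in Aim 1", and no term that switches on when waitlist participants start the programme. Aim 3 is described only as similar to Aim 2, with a logit link.

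**Status of the linear form.** The same section calls intercept plus linear change an assumption for the rest of the text. The final time form is to be explored in the random comparison sample, with further power analyses before the choice is made.

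**The concern.** By T5 both CBO arms are in or past RIWP, so T5 no longer compares treated with untreated people. T5 also has the highest leverage on a straight line. RIWP is a 16-week programme given once, early in follow-up. If its benefit appears early and lasts, the arm difference opens after T1 and narrows again when the waitlist arm is treated. A single slope reads that shape as little or no change, and the benefit moves into B01, where it looks like a baseline imbalance. Aim 1 is described as the principal objective, and its power is presented as strong and conservative.

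Aim 2 has a related problem. If RIWP is coded by assigned arm there as well, treated waitlist participants at T5 carry RIWP = 0 and CBO = 1, so any gain from RIWP enters the CBO terms that answer Aim 2.

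**Working it through.** **Inputs from the protocol.** 150 per arm; 10% attrition in the CBO sample, so 150 × .9 = 135 per arm; baseline-posttest correlation .68; d = .30; stated Aim 1 power .91.

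**Assumed, because the protocol does not give them.** Two-sided alpha .05; a five-wave covariance (compound symmetry unless stated). Benefit is written as positive.

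**1. The stated power.** With baseline adjustment the residual SD is √(1 − .68²) = .733. The standard error is .733 × √(2/135) = .0892, and z = .30/.0892 = 3.36. Power = Φ(3.36 − 1.96) = .92, which agrees with .91. This figure is for a pre/post contrast.

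**2. Where T5 falls.**
- Months counted from study start: T1 precedes RIWP in Month 5, so T1 is in about Months 1-4, T4 in Months 25-28 and T5 in Months 33-36.
- Months counted from T1: T4 is Month 24 and T5 is Month 32.
- On both readings T4 precedes Month 29, and T5 falls within Months 29-35 or just after.

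**3. Equal lags.** T2 comes 4-7 months after Month 5 (Months 9-12) on the first reading, or 3 months after it on the second. T5 comes 4-7 months, or 3 months, after Month 29. The same fraction a of the effect should therefore apply to the RIWP arm at T2 and to the waitlist arm at T5.

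**4. Slope over five waves.** The arm difference is (0, ad, d, d, (1−a)d). With wave scores −2, −1, 0, 1, 2 (sum of squares 10):

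slope = [−ad + d + 2(1−a)d]/10 = 0.3(1−a)d per wave.

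At a = 1 the profile is (0, d, d, d, 0), the slope is 0 and the fitted baseline term B01 is 3d/5 = 0.6d, or .18 for d = .30. The zero also holds under AR(1) and with a random slope.

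**5. Two comparators.**
- Five waves with no crossover, profile (0, ad, d, d, d): slope = (−ad + d + 2d)/10 = (0.3 − 0.1a)d.
- T1-T4 only, profile (0, ad, d, d), scores −1.5 to 1.5 (sum of squares 5): slope = (−0.5a + 0.5 + 1.5)d/5 = (0.4 − 0.1a)d.

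**6. Power for d = .30.** The residual variance is 1 − .68 = .32. The SE per wave is √(2 × .32/135/10) = .0218 for five waves and √(2 × .32/135/5) = .0308 for T1-T4.

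| a | Five waves, as scheduled: slope, power | Five waves, no crossover: slope, power | T1-T4: slope, power |
|---|---|---|---|
| 0 | .090, .99 | .090, .99 | .120, .97 |
| .5 | .045, .54 | .075, .93 | .105, .93 |
| 1 | 0, .05 | .060, .79 | .090, .83 |

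At a = .2 the five-wave slope is .072, z = .072/.0218 = 3.3 and power is .91. The stated power is therefore reached only if a is about .2 or less.

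**7. Sensitivity of the T1-T4 figure at a = 1.** .83 under compound symmetry; .78 with a random slope (intercept variance .68, slope variance .01, residual .32); .55 under AR(1) with .68.

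**The case against.** **The model is provisional.** The protocol says that the best longitudinal approach is not known in advance, lists piecewise change among the alternatives, mentions mean post-baseline levels as a one-parameter example, and promises more power work and simulations. A reader might infer that the principal test is biased toward no effect by design. The text does not support that: B03 is the only test written down, but it is not final, and use of all five waves is inferred from the absence of any exclusion. What remains is that a time shape chosen in people with no treatment effect and no waitlist neither removes post-crossover observations nor recodes exposure. The promised simulations could reveal the problem, but the protocol does not say that they will include the crossover.

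**Exactly zero is a corner case.** It needs the full effect by T2, full persistence and full waitlist catch-up by T5. A reader might also pair half catch-up at T5 with the full effect at T2, which gives power of .28. The protocol's own months place T2 and T5 at the same lag after each arm's start, so the consistent half-effect figure is .54.

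**Sign reversal.** If the waitlist arm were treated before T4, the slope could change sign. That conflicts with Months 29-35, which follow T4.

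**Three timepoints.** At 8-month spacing, two years spans four surveys (0, 8, 16, 24 months), whereas three surveys span 16 months. A reader might call this a proven contradiction. It can also mean three follow-ups (8, 16, 24 months), which fits two years and a Month 29 start. It is loose wording that needs clarifying.

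**The effect may not be a step.** The protocol frames it as a slope difference. If nothing has appeared by T2 (a = 0), the five-wave slope loses nothing to the crossover.

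**Conclusion.** The point holds in this form: the written Aim 1 test mixes randomized and post-crossover observations, and no provision in the protocol separates them. For an early, sustained benefit of .30 SD, the crossover alone lowers the power of the five-wave slope test from .93 to .54 when half the effect is present at T2 and T5, and from .79 to .05 when all of it is. The claim that the pre/post .91 is conservative therefore does not carry over to B03 over five waves unless a is about .2 or less. These figures rest on a sustained effect, equal lags in the two arms, 135 per arm, correlation .68, compound symmetry and two-sided alpha .05. Only the zero slope at a = 1 was the same under every covariance tried. For Aim 2 the missing time-varying exposure is visible in the equation. For Aim 3 it is inferred from the stated similarity to Aim 2.

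**What to change.** 1. State that the confirmatory Aim 1 contrast uses only waves observed before the waitlist arm starts RIWP, whatever time form is later chosen. On the Months 29-35 schedule these are T1-T4. Report T5 separately as post-crossover.
2. In the Aim 2 and Aim 3 models, code RIWP exposure as time-varying (0 for everyone at T1, 1 for waitlist participants once they have started), or drop their post-crossover observations.
3. Recompute Aim 1 power for the contrast actually chosen, with the covariance stated. For a linear slope on T1-T4 the range above is .55 to .83 at a = 1, so the choice of time form still matters.
4. Reconcile the references to two years, three timepoints and Months 29-35.

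The cost is wording and a new power calculation, with no added participants or surveys. T5 no longer contributes to the randomized contrast. Under compound symmetry that loses a little power only when a is near 0 (.97 against .99).
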